#### Exclusion criteria

History of drug dependence or alcohol addiction.Severe central nervous system diseases or other systemic diseases such as cardiovascular and cerebrovascular conditions.Organic lesions such as craniocerebral trauma.Inner ear or auditory nerve diseases such as sudden deafness, Meniere’s disease, otosclerosis, or auditory neurinomas.External ear or middle ear related diseases such as otitis externa, acute/chronic otitis media.Patients with auditory hyperacusis.

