Given the significant potential of fNIRS and ABR in tinnitus research, and the constraints of prior studies, we have developed this randomized controlled experiment (RCT) to investigate the pathological mechanisms of chronic tinnitus using fNIRS and ABR. The objectives of this trial are: (1) To compare the auditory brainstem response parameters and extracerebral oxygen levels of the cerebral cortex between chronic tinnitus patients and healthy subjects, and to compare the correlation of peripheral-central auditory function under different physiological states. (2) To compare the intervention effects of acupuncture versus sham acupuncture on chronic tinnitus patients from clinical manifestations, ABR parameters, and extracerebral oxygen levels of the cerebral cortex, exploring the correlation of acupuncture intervention on chronic tinnitus from the peripheral-central auditory function at three levels: clinical, target organ, and central.

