#### Inclusion criteria for healthy subjects

Individuals aged between 20 and 55 years, who are right-handed.All physiological indicators are within the normal range upon physical examination, with no history of functional or organic diseases, and no head injuries.No family history of psychiatric or neurological genetic diseases.The subject signs a paper version of the informed consent form, volunteering to participate in this trial.

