### Concurrent intervention and care

During the time frame for studying, Subjects are instructed to avoid engaging in any additional interventions which may influence the study outcomes, including, but not restricted to, medicine and behavioral treatment. If participants undergo other combined interventions for tinnitus, researchers must document pertinent facts for future examination. Nevertheless, for participants with comorbidities include hypertension, diabetes, and various other chronic conditions, they may persist with their standard medication and therapies. Researchers will document the identities of these comorbidities, drugs, and therapy in the case type of report.

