### Outcome measures

Clinical Results: Clinical result metrics encompass the Tinnitus Handicap Inventory (THI), ABR testing, and fNIRS data collection. Evaluations will be carried out at baseline, after 10 treatment sessions.

THI score: The THI is a self-reported checklist that’s quick, simple. To manage and interpret, and covers a wide range of issues. It consists of 25 items, each scored from 0 to 4. An elevated THI indicates a more severe level of tinnitus.

ABR testing: The test records the peak latencies (PL), wave amplitudes, and interpeak intervals (IPL) of the subjects at various stimulation rates, as well as the differences in PL and IPL at the two stimulation rates (ΔPL and ΔIPL) to evaluate the function of the peripheral auditory nerve.

fNIRS data acquisition and processing: Cortical blood oxygen data will be collected to evaluate the central function of the subjects.

fNIRS results: fNIRS scans will be conducted at baseline, and after 10 treatment sessions. The blood oxygen concentrations measured include the concentrations of oxygenated hemoglobin (HbO), hemoglobin that has lost oxygen (HHb), and total hemoglobin (THb) in every measured channel.

fNIRS functional connectivity intensity: The intensity of functional connectivity between regions can quantify the relationships between routes or areas of interest within the fNIRS time plots. This is computed using the Pearson correlation coefficient between the average time series of any pair of channels of interest. The functional connectivity strength between channels of interest, as well as between channels of interest and other channels, is computed using NIRSKIT software. This software will help in analyzing the correlation between the time series data from different channels, providing insights into the connectivity patterns within the brain that may be associated with tinnitus and its treatment.

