### Analytical statistics

Date analysis will be done using SPSS version 26 (IBM Corporation, Armonk, NY, 2019), with a two-sided significance threshold established at 0.05. In terms of data description, continuous data is presented as mean ± standard deviation (x ± s), and categorical and ordinal data is stated as proportions (%). The intervention effects will be represented by OR and 95% CI. Data on immediate and cumulative effects of the two acupuncture groups, clinical scoring, ABR parameter analysis, and fNIRS data analysis is compared using T-tests. Permutation tests will be used, and multiple comparisons will be examined using False Discovery Rate (FDR) correction. The differences in THI scores, ABR parameters, and functional values of brain regions will be analyzed for correlation using Pearson’s correlation analysis, with inspection level *α* = 0.05.

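### Eligibility wording leaves open whether patients with vascular or metabolic disease may enrol; if they may, the patient-versus-healthy fNIRS comparison in objective 1 is open to confounding of unknown size.

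*Protocol article*

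**What the plan says.** Three eligibility and care statements in the protocol article bear on this point.

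- **Exclusion criteria (patients):** "Severe central nervous system diseases or other systemic diseases such as cardiovascular and cerebrovascular conditions".
- **Concurrent intervention and care:** "for participants with comorbidities include hypertension, diabetes, and various other chronic conditions, they may persist with their standard medication and therapies". The section adds: "Researchers will document the identities of these comorbidities, drugs, and therapy in the case type of report".
- **Inclusion criteria for healthy subjects:** "All physiological indicators are within the normal range upon physical examination, with no history of functional or organic diseases, and no head injuries".

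Objective 1, at the end of the Introduction, is to "compare the auditory brainstem response parameters and extracerebral oxygen levels of the cerebral cortex between chronic tinnitus patients and healthy subjects". The fNIRS outcomes are oxygenated, deoxygenated and total haemoglobin per channel, and functional connectivity derived from those signals. Under Analytical statistics, "clinical scoring, ABR parameter analysis, and fNIRS data analysis is compared using T-tests", with permutation tests, false discovery rate correction and Pearson correlation also named. That sentence opens with the two acupuncture groups, but the article gives no other method for comparing patients with healthy subjects. It states no matching, restriction or adjustment for comorbidity or medication.

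**The concern.** Hypertension is a cardiovascular condition and diabetes a systemic disease. Depending on what 'Severe' qualifies, the exclusion list either bars such patients or admits those below a severity threshold that is not given. Two screeners could therefore decide differently on the same treated hypertensive patient.

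The statistical stake lies in objective 1. The Introduction says that fNIRS records haemodynamic activity and infers neural activity from it. If vascular or metabolic disease, or the drugs for it, shifts the haemoglobin signal, a patient-healthy difference could arise without any difference in neural activity due to tinnitus. The healthy group is free of such disease by rule and the patient group may not be, so the imbalance would be built into recruitment. False discovery rate correction deals with multiplicity and does nothing about it.

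**Working it through.** No figure in the article depends on this point, so there is none to reproduce. The check is a comparison of texts, followed by an illustration on assumed inputs.

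**1. The two readings side by side**

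| | 'Severe' governs only nervous-system disease | 'Severe' governs both items |
|---|---|---|
| Hypertension or diabetes in patients | excluded | eligible, with no stated threshold |
| Fit with the concurrent-care section | conflict: it plans for patients who cannot enrol | consistent |
| Hypertension or diabetes in healthy subjects | excluded | excluded |
| Imbalance in objective 1 from this source | largely absent | possible, on the patient side only |

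Each reading leaves one problem, and not the same one. The concurrent-care section points to the second column.

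**2. Inputs for the illustration**

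- Patients: 72 (Study design). I assume that all of them enter objective 1; the flow charts are not shown.
- Healthy subjects: 15 (Sample size estimation).
- Two-sided alpha: 0.05 (Analytical statistics).
- Share p of patients with a vascular or metabolic condition: not given; assumed 5% to 30%.
- Shift d in an fNIRS outcome caused by the condition or its drugs, in SD units: not given; assumed 0.3 to 0.8.

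**3. Formulas**

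- Bias = p × d, since the share in healthy subjects is 0 by rule.
- SE = √(1/72 + 1/15) = √(0.0139 + 0.0667) = 0.284 SD.
- False-positive rate = Φ(bias/SE − 1.96) + Φ(−bias/SE − 1.96), by normal approximation, for one outcome with no true tinnitus effect.

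**4. Results**

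| p | d (SD) | Bias (SD) | False-positive rate |
|---|---|---|---|
| 5% | 0.3 | 0.015 | 5.0% |
| 10% | 0.5 | 0.05 | 5.4% |
| 20% | 0.5 | 0.10 | 6.4% |
| 30% | 0.8 | 0.24 | 13.5% |

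The distortion runs from negligible to material, and the article gives nothing that places the trial within that range.

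**5. Precision cost of restriction**

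Suppose that 18 of the 72 patients (25%, assumed) are set aside, leaving 54:

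- SE = √(1/54 + 1/15) = √(0.0185 + 0.0667) = 0.292 SD.
- Ratio: 0.292/0.284 = 1.03, about 3% larger.

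The loss is small because the 15 healthy subjects supply 0.0667 of the 0.0806 total variance with all patients included, or 83%.

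**The case against.** The strongest reply is that the exclusion criterion is merely loosely worded. The word 'other' ties the two disease classes together, so 'Severe' naturally covers both, and the concurrent-care section then fits: severe systemic disease is out and stable chronic disease is in. That is a fair reading, and it is why a flat contradiction, which a reader might infer, is not established. It also means that the two problems cannot both apply in full: a strict exclusion largely removes the confounding, and a lenient one removes the conflict.

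Four further points have weight.

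- **Size.** The material figure of 13.5% needs a 30% share and a 0.8 SD shift, both assumed. A count of affected patients from an assumed prevalence would not measure bias either.
- **Scope.** The article lists the THI, ABR and fNIRS together and ranks none as central. The haemodynamic argument reaches only the fNIRS part.
- **Preprocessing.** The plan filters out physiological interference. Filtering of that kind cannot be assumed to remove a lasting difference between groups caused by disease or medication.
- **Unseen plan.** Adjustment could sit in an analysis plan that is not shown, so its absence alone is no finding.

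What still stands is what the article itself fixes: different health standards for the two groups, an unclear patient criterion, and a comparison of a haemodynamic signal between those groups. The limitations in the Discussion name variation in tinnitus severity but not comorbidity.

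**Conclusion.** The point holds in limited form. The Exclusion criteria and the concurrent-care section conflict on one reading and must be reconciled; this review does not say which eligibility rule is right. On the reading that the concurrent-care section supports, the objective 1 fNIRS comparison is open to confounding by vascular and metabolic disease and its medication. The size is unknown: a bias of 0.015 to 0.24 SD over the assumed inputs shown.

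Two stronger conclusions are not supported. The first is that the comparison is confounded: that needs a comorbidity share and an effect on the signal, and the article gives neither. The second is that the acupuncture-sham comparison is biased: 1:1 randomisation balances comorbidity between the arms in expectation, and the article offers no figure for any added variability.

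**What to change.** 1. Reconcile the two sections. State in the Exclusion criteria whether 'Severe' applies to systemic and cardiovascular disease, and make the concurrent-care section name only comorbidities that the criteria admit.
2. If such patients remain eligible, prespecify for the objective 1 fNIRS comparison a second analysis restricted to patients with no recorded vascular or metabolic comorbidity and no vasoactive medication. Report it beside the all-patient result, with estimates and confidence intervals for both.
3. Attribute a patient-healthy fNIRS difference to tinnitus only if it persists in the restricted analysis. This condition is necessary but not sufficient, since the comparison remains non-randomised.

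The cost is one reworded criterion, an aligned care section and one extra analysis. The comorbidities and drugs are already to be recorded, so no new data are needed. The restricted analysis is slightly less precise, by about 3% in standard error under the assumed 54 patients. The all-patient result is kept, so nothing is lost from it.

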#### Inclusion criteria for healthy subjects

Individuals aged between 20 and 55 years, who are right-handed.All physiological indicators are within the normal range upon physical examination, with no history of functional or organic diseases, and no head injuries.No family history of psychiatric or neurological genetic diseases.The subject signs a paper version of the informed consent form, volunteering to participate in this trial.

#### Exclusion criteria for healthy subjects

Pregnant or breastfeeding women, or those who plan to conceive within the next 6 months.Individuals with a history of head trauma.No metallic implants in the body and no contraindications for fNIRS testing.Those who are taking part in more clinical studies at the moment.

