#### Inclusion criteria

Patients with chronic tinnitus, defined as a duration of the tinnitus of 6 months or longer (2).No contraindications for fNIRS scanning.Individuals aged between 20 and 55 years, who are right-handed.Patent external auditory canal and intact eardrum.The average hearing threshold in both ears is less than 35 dB.Normal expressive and comprehension abilities.

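### The healthy-volunteer metal/fNIRS exclusion is printed the wrong way round, and controls have no explicit ear, hearing or tinnitus criteria, which leaves the patient-versus-healthy comparison open to confounding

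*Protocol article*

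**What the plan says.** All references are to the Protocol article.

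- **Exclusion criteria for healthy subjects** include "No metallic implants in the body and no contraindications for fNIRS testing". The other items in that list (pregnancy or planned conception, head trauma, taking part in other studies) name conditions that bar entry.
- **Inclusion criteria** for patients contain the corresponding item, "No contraindications for fNIRS scanning".
- **Ear and hearing rules for patients.** The inclusion list requires "Patent external auditory canal and intact eardrum" and "The average hearing threshold in both ears is less than 35 dB". The exclusion list removes "Inner ear or auditory nerve diseases such as sudden deafness, Meniere’s disease, otosclerosis, or auditory neurinomas", and also external-ear disease, middle-ear disease and hyperacusis.
- **Inclusion criteria for healthy subjects** give one general health rule: "All physiological indicators are within the normal range upon physical examination, with no history of functional or organic diseases, and no head injuries". They also require age 20 to 55 and right-handedness, as for patients.
- **Introduction**, first objective: "To compare the auditory brainstem response parameters and extracerebral oxygen levels of the cerebral cortex between chronic tinnitus patients and healthy subjects".
- **Allocation concealment and randomization** stratifies by gender and age (printed as lifetime), for the two randomised patient arms only.
- **Sample size estimation** plans 72 patients and 15 healthy subjects.

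**The concern.** There are two separate points.

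First, one eligibility rule says the opposite of what it must mean. Anyone screening volunteers from the printed list would have to reject suitable people or depart from the text.

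Second, the two groups in the first objective are selected by different rules on the organ being measured. The Introduction describes ABR as reflecting activity from the cochlea to the brainstem, and links wave I amplitude to cochlear synapses and nerve fibres as well as to tinnitus symptoms. A difference between the groups in the state of the ear could therefore appear in the parameters that are to be read as a tinnitus effect. The controls are not randomised against the patients, so nothing in the design balances hearing, age or sex between them. If control hearing is not recorded at the time, a difference cannot be recovered afterwards.

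**Working it through.** **The inverted item.** An entry in an exclusion list names a state that bars entry. Here the state is having no metal implants and no fNIRS contraindication, so the literal rule bars volunteers who can be scanned. The patient list uses almost the same words about fNIRS under inclusion, where they make sense. This settles the intended direction.

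**The two lists side by side.**

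| Item | Patients | Healthy subjects |
|---|---|---|
| Age 20–55, right-handed | stated | stated |
| Mean hearing threshold | below 35 dB, both ears | none stated |
| Canal and eardrum | stated | none stated |
| Inner-ear, nerve, outer- and middle-ear disease | excluded | not named; general no-disease rule |
| Hyperacusis | excluded | not named; general no-disease rule |
| Tinnitus | required | absence not named; general no-disease rule |
| Balance on gender and age | stratified between the two arms | no matching to patients stated |

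The general rule "All physiological indicators are within the normal range upon physical examination" can be read in two ways. If it covers hearing, controls hear normally while patients may average anything below 35 dB. If it does not, control hearing is unknown. Under either reading the groups may differ in hearing.

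**The plan's own figure.** The plan gives a minimum of 12 healthy subjects and recruits 15. Inflating 12 by a 20% loss gives 12/(1 − 0.20) = 15. The 20% is borrowed from the patient arms, since no loss rate is stated for controls. The figure of 15 is not in dispute.

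**Chance imbalance with 72 and 15** (assuming both groups come from one population):
- Sex, assuming 50% women: an exact binomial sum gives a gap of at least 20 percentage points in about 16% of samples.
- Age, assuming a uniform spread over 20–55: SD = 35/√12 = 10.1 years; SE of the difference = 10.1 × √(1/15 + 1/72) = 2.87 years; a mean gap of at least 5 years has z = 5/2.87 = 1.74, or about 8% of samples.

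**What an imbalance would do.** Suppose it shifts an ABR parameter by d SD with no tinnitus effect, and the groups are compared by an unadjusted two-sided t-test at 0.05. The noncentrality is d × √(n × 15/(n + 15)). For n = 72 this is d × √(1080/87) = 3.52d on 85 df. The text does not say how many patients enter this comparison, so smaller numbers are shown too.

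| Assumed shift d | 72 vs 15 | 36 vs 15 | 15 vs 15 |
|---|---|---|---|
| 0.2 SD | 10.7% | 9.8% | 8.3% |
| 0.3 SD | 18.1% | 16.0% | 12.5% |
| 0.5 SD | 41.4% | 35.8% | 26.2% |

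The documents hold no hearing, age or sex data, so the true d cannot be computed. The table shows only how a bias would act if present.

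**The case against.** The strongest case on the other side has five parts.

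- **The inversion is a slip that no site would apply literally.** That is likely, and the patient list supports it. It is still the operative text and should be corrected. A reader might infer that it feeds the ABR confounding. It does not: it concerns who may be scanned, and is a separate point.
- **A group called healthy with no functional or organic disease would naturally exclude tinnitus and ear disease.** This is a fair reading and weakens the tinnitus gap. It still sets no audiometric limit and names no ear examination, although the patient list in the same article does both.
- **Matching and adjustment may be in a full protocol or analysis plan that is not shown.** This stands, so their absence is not called an error. The eligibility lists are printed item by item and can be judged.
- **The rejection rates assume the bias they illustrate.** This also stands. The t-test sentence in Analytical statistics refers to the two acupuncture groups, so an unadjusted test of 72 against 15 is itself an assumption.
- **Adjusting for hearing could remove part of what is being studied.** The Introduction treats the cochlea as the starting site of tinnitus, so a hearing difference may belong partly to the condition. This argues against hearing adjustment as the main analysis. Nor would a shared upper limit make hearing equal in the two groups.

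**Conclusion.** (a) The metal/fNIRS item for healthy subjects is wrong as written. This is certain from the text and takes one line to correct.

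(b) The patient-versus-healthy ABR and fNIRS comparison is open to confounding by hearing, age and sex, because ear and hearing rules are explicit for patients only and no age or sex balance is stated within the shared band. This is an inexpensive improvement to make, not a demonstrated bias.

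A reader might infer that the comparison is already confounded. The documents do not support that: they show no imbalance, both groups share the age band and right-handedness, and the size of any bias cannot be derived. The rates of about 11%, 18% and 41% rest on assumed shifts of 0.2, 0.3 and 0.5 SD, on 72 against 15 subjects, and on an unadjusted t-test. The randomised acupuncture-versus-sham comparison is unaffected by either point.

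**What to change.** 1. In the exclusion criteria for healthy subjects, reword the item to metallic implants or any contraindication to fNIRS testing. Alternatively, move it to the inclusion list, as for patients.
2. Add to the inclusion criteria for healthy subjects: no current or past tinnitus, the same canal, eardrum and ear-disease criteria as patients, and a recorded hearing threshold within the patients' limit.
3. Frequency-match the 15 controls to patients on gender and age band, or adjust the patient-versus-healthy comparison for age and sex. Report adjustment for hearing threshold as a sensitivity analysis, because part of the peripheral difference may belong to tinnitus.

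The cost is amendment wording, a brief hearing check for 15 volunteers who already attend for ABR, and slightly slower recruitment of controls.

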#### Allocation concealment and randomization

Suitable participants will be assigned at random to the acupuncture group or the sham acupuncture group in a proportion of 1:1 using a random stratification block design by gender and lifetime, with the Statistical Product and Service Solutions Version 25.0 (SPSS Inc., Chicago, IL, USA). An impartial administrator, uninvolved in other study protocols, will conduct this process, and the details of the list of random allocations will remain completely confidential. This randomization results will be preserved in opaque, sealed, envelopes with sequential numbers to guarantee allocation concealment.

